# End-on versus parallel radiofrequency lesioning for neurotomy of the cervical medial branch nerves: a study protocol of a prospective, randomized, double-blind clinical trial: the “EndPaRL” study

**DOI:** 10.1186/s13063-023-07752-9

**Published:** 2023-11-11

**Keywords:** Neck pain, Cervical medial branch nerve, Radiofrequency ablation, Pain, Non-inferiority

## Abstract

**Background:**

Cervical facet joint disease is a common source of neck pain and its prevalence increases with aging. Conservative multimodal management options (e.g., strengthening of neck muscles, non-steroidal anti-inflammatory medications, massage, and thermal modalities) often fail to relieve pain. Cervical medial branch nerve (CMBN) radiofrequency neurotomy (RFN) is an effective minimally invasive technique for treating chronic neck pain secondary to facet joint disease. An end-on approach for this procedure has been proposed that may be technically easier and require less time while reducing post-procedural discomfort. The protocol presented here is for a study that aims to compare the efficacy of a new end-on approach using multi-tined cannulae, against the conventional parallel technique that employs straight cannulae for RFN of the CMBN in patients with chronic neck pain due to cervical facet joint disease.

**Methods:**

A multicentre randomized, non-inferior, active comparator-controlled trial will be conducted with two parallel groups and blinding of participants and outcome assessor. The study will include 72 adults with chronic neck pain secondary to facet joint disease who are candidates for RFA of the CMBN. Participants will be randomized to either the conventional parallel or the end-on approach in a 1:1 ratio. The intensity of pain and pain-related domains (function, quality of life, sleep, adverse effects of the interventions, analgesic intake) will be measured at 1, 3, 6, and 12 months after the procedure.

**Discussion:**

Neck pain secondary to cervical facet joint disease is prevalent and RFA of the CMBN is a validated treatment for relieving it. The conventional parallel technique can be technically challenging, and it can be associated with adverse effects while the newer end-on approach has the potential of being a simpler technique with less adverse effects. This trial will be the first non-inferiority study to compare the clinical efficacy of the end-on approach against the conventional parallel approach for RFN of CMBN in patients with chronic neck pain due to cervical facet joint disease.

**Trial registration:**

ClinicalTrials.gov NCT05818774. Registered on April 20, 2023.

**Supplementary Information:**

The online version contains supplementary material available at 10.1186/s13063-023-07752-9.

## Administrative information

World Health Organization Registration Data Set

## Introduction

### Background and rationale

Parallel radiofrequency neurotomy (RFN) of the cervical medial branch nerves (CMBN) utilizing sharp straight needles was first demonstrated to be clinically efficacious in a randomized clinical trial (RCT) setting for the treatment of chronic neck pain following whiplash injury almost three decades ago [1]. Over the next 20 years, several other studies followed with variable success rates. In the early 2000s, in a consecutive series of cases, the authors reported a success rate (defined as the complete abolition of pain) of 46 and 26% following RFN of the CMBN at 6 and 12 months, respectively [2]. Previously, an observational study in the late 1990s had already reported a success rate (defined as abolition of pain) of 57 and 36% at the 6- and 12-month follow-up, respectively [3]. Later, in 2012, a study conducted in New Zealand reported a success rate (defined as greater than 80% pain relief) of 68 and 51% at 6 and 12 months post-procedurally, respectively [4]. In addition, the rate of complications between studies also showed variability throughout the years. The rates of temporary post-procedural dysesthesias have been noted to vary from 43 to 67%, while the rates of temporary cutaneous numbness have been reported to range between 36 and 58%. Of note, only the rates of post-procedural pain seem to be relatively concordant between authors, with reported rates varying between 95 and 100% among studies. This data was comprehensively analyzed in a systematic review published in the late 2010s by the Standards Division of the Spine Intervention Society (SIS), where the authors looked at the effectiveness and risks of fluoroscopically guided parallel (also called conventional) RFN of the CMBN [5].

More recently, multi-tined trident cannulae have been developed that allow for end-on lesioning of the medial branch nerves. In a recent ex vivo study, multi-tined trident cannulae with a distal deployment mechanism demonstrated stable lesion characteristics at varying approach angles to the periosteal plane, while conventional sharp curved and 2-tined sharp straight cannulae did not [6]. The authors demonstrated that the trident cannulae created a pyramidal lesion closest to the tip that could create a stable lesion size up to an angle of 90° to the periosteal surface. Later, in a retrospective study, the authors reported that RFN of the CMBN with multi-tined trident cannulae conferred greater pain relief at 2 months post-procedure, as well as shorter procedure and fluoroscopy times when compared to lesioning with sharp straight conventional and 2-tined sharp straight cannulae [7].

### Rationale

The ex vivo study by Finlayson et al. [6] and the clinical retrospective study [7] provided pre-clinical and clinical evidence, respectively, that multi-tined trident cannulae may provide more consistent clinical results when utilized in the setting of RFN of the CMBN in patients with neck pain secondary to cervical facet joint disease. However, high-quality clinical evidence from an adequately powered study is required to evaluate the clinical outcomes of RFN of the CMBN utilizing an end-on approach with multi-tined trident cannulae, as compared to utilizing a parallel approach with a conventional sharp straight needle (the recommended SIS technique). The proposed *End*-on Versus *Pa*rallel *R*adiofrequency *L*esioning for Neurotomy of the Cervical Medial Branch Nerves (the EndPaRL study) will be the first prospective, randomized, outcome assessor-blinded, clinical trial comparing the clinical efficacy of sharp straight conventional versus multi-tined trident cannulae for RFN of the CMBN in patients with chronic neck pain due to cervical zygapophyseal joint osteoarthritis. The results of this study will help understand the role, benefits, and adverse effects of end-on lesioning techniques for RFN of the CMBN in the context of moderate-to-severe cervical zygapophyseal joint osteoarthritis while comparing this technique to the conventional parallel RFN approach.

### Objectives

The aim of our trial is to compare the efficacy of the recommended SIS technique utilizing a conventional parallel approach against the end-on approach for RFN of the CMBN in patients presenting with chronic, moderate-to-severe, neck pain in the context of cervical facet joint disease. The following are the primary objectives of this trial:To compare the difference in mean Numerical Rating Scale (NRS) for pain scores at 3 months after the study interventions.To compare the proportion of patients with a positive analgesic response (defined as 50% or greater reduction in the NRS score for neck pain as compared to baseline) at 3 months after the study interventions.

The following are the secondary objectives:To compare the difference in mean NRS for pain scores at 1, 6, and 12 months after the study interventions.To compare the proportion of patients with a positive analgesic response at 1, 6, and 12 months after the study interventions.To compare the proportion of patients with 10 points or greater reduction in the Neck Disability Index (NDI) score (the minimal clinically important difference (MCID) [8]) at 1, 3, 6, and 12 months after the study interventions.To compare the proportion of participants reporting some or much improvement in the Patients’ Global Impression of Change (PGIC) scale at 1, 3, 6, and 12 months after the study interventions [9].To compare the mean Pittsburgh Sleep Quality Index (PSQI) scores and EuroQol (EQ-5D-5L) scores at 1, 3, 6, and 12 months after the study interventions [10].To compare the duration of performing the study interventions, patient discomfort, radiation dose, and cost of the study interventions.To compare average physical activity and sleep duration as measured by wrist-worn actigraphy over 1 week before the procedure and 1-month follow-up after the study interventions.To assess the incidence of peri-procedural complications and post-procedural adverse effects during and at 1, 3, 6, and 12 months after the study interventions.To assess opioid requirements in daily oral morphine equivalents in milligrams averaged over the 1 week prior to the 1-, 3-, 6-, and 12-month follow-ups after the study interventions.To assess the patient assumption of the group they were assigned to at 3-month follow-up after the study interventions.

### Hypotheses

The primary hypotheses for this non-inferiority trial are that end-on lesioning for RFN of the CMBN is non-inferior to the parallel conventional technique for its impact on the intensity of pain relief and the proportion of patients with a positive analgesic response at 3 months after the intervention in patients with chronic, moderate-to-severe neck pain in the context of cervical zygapophyseal joint syndrome. The secondary hypotheses are that end-on lesioning for RFN of the CMBN is non-inferior to the parallel conventional technique for its impact function, quality of life, sleep, adverse effects of the interventions, analgesic intake at specified time points within 1 to 12 months after the interventions in patients with chronic, moderate-to-severe neck pain in the context of cervical zygapophyseal joint syndrome.

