### Outcomes

Patients will be assessed at baseline and 1, 3, 6, and 12 months after the study interventions. The assessment schedule and parameters are summarized in Table 2.

**Table 2 Tab2:** EndPaRL assessment schedule

**Outcome**	**Measure**	**Baseline**	**Immediate after procedure**	**1 month after procedure**	**3 months after procedure**	**6 months after procedure**	**12 months after procedure**
**Patient demographics**		**X**					
**Pain intensity**	NRS	**X**	**X**	**X**	**X**	**X**	**X**
**Neck disability**	NDI	**X**	**X**	**X**	**X**	**X**	**X**
**Global improvement**	PGIC			**X**	**X**	**X**	**X**
**Sleep quality**	PSQI	**X**		**X**	**X**	**X**	**X**
**Sleep duration**	In hours and minutes from actigraphy device	**X**		**X**			
**Physical functioning**	Time spent at different activity levels from actigraphy device^b^	**X**		**X**			
**Opioid intake**	Daily OME in mg	**X**		**X**	**X**	**X**	**X**
**Analgesics**	Name and dose	**X**		**X**	**X**	**X**	**X**
**Procedure** **(1) Duration** **(2) Cost** **(3) Discomfort** **(4) Radiation**	(1) In minute (2) In CAD (3) 0–10 (4) Dose in mSv		**X** **X** **X** **X**				
**Complications**	e.g., bleeding, hematoma		**X**				
**Adverse effects**				**X**	**X**	**X**	**X**
**Health-related quality of life**	EQ-5D-5L^a^	**X**		**X**	**X**	**X**	**X**

*CAD* Canadian dollars, *NRS* Numerical Rating Scale, *OME* Oral morphine equivalents

^a^EuroQol 5-level EQ-5D version (EQ-5D-5L); Neck Disability Index (NDI); Numerical Rating Scale (NRS); Patients’ Global Impression of Change (PGIC); Pittsburgh Sleep Quality Index (PSQI)

^b^Data on physical activity and sleep collected using participant-worn actigraphy devices (light/moderate/severe)

The following are the *primary outcomes*:The between-group difference in mean NRS for pain intensity scores at 3 months after the interventions.The between-group difference in the proportion of patients with a positive analgesic response (defined as 50% or greater reduction in the NRS score for neck pain as compared to baseline) at 3 months after the interventions.

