### Sample size

The sample size was calculated using the Statistical Package for the Social Sciences (SPSS, IBM SPSS Statistics) software. A sample size of 72 participants (36 in each treatment group) will provide 80% power to detect a difference (inferiority margin), at 3 months after the intervention, in the mean NRS pain intensity scores (0–10 scale) between the two treatment groups being less than or equal to 1 point, given a standard deviation (SD) of 1.7 at the 0.05 significance level (alpha) using a two-sided two independent sample *t*-test. To satisfy both the non-inferiority and superiority hypothesis, we plan to recruit a total of 80 participants to account for a presumed 10% dropout rate. The sample size calculations and the assumptions underlying it are based on data published on RFN of nerves supplying other axial joints (lumbar facets, sacroiliac) for the relief of spinal pain [12, 13]. The chosen non-inferiority margin of less than or equal to 1 point (10%) is reasonable because a minimal clinically important difference in pain scores for a treatment to be considered efficacious is 2 points or 30% [14]. A non-inferiority study is justified to compare the end-on and parallel RFN lesions because similar efficacy is expected but there may be a lower incidence of adverse effects (e.g., patient discomfort) and better resource utilization (e.g., faster procedure time, lower radiation dose) with the end-on RFN technique.

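### The 3-month responder proportion is a primary non-inferiority outcome, but it has no margin, no sample-size basis and a planned test of difference that cannot show non-inferiority

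*Protocol article*

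**What the plan says.** The Protocol article names the responder proportion as primary in three places. Objectives lists it as the second primary objective. Hypotheses describes end-on lesioning as "non-inferior to the parallel conventional technique for its impact on the intensity of pain relief and the proportion of patients with a positive analgesic response", with 3 months as the time point. Outcomes gives the second primary outcome as "The between-group difference in the proportion of patients with a positive analgesic response (defined as 50% or greater reduction in the NRS score" from baseline), again at 3 months.

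Sample size deals with the other primary outcome only. The difference it is built on is "in the mean NRS pain intensity scores (0–10 scale) between the two treatment groups being less than or equal to 1 point". The *t*-test calculation behind it is described as "given a standard deviation (SD) of 1.7 at the 0.05 significance level (alpha) using a two-sided two independent sample". Its one statement on the margin is "The chosen non-inferiority margin of less than or equal to 1 point (10%) is reasonable", which is argued from a minimal important difference in pain scores. The result is 72 participants, 36 per group, for 80% power, raised to 80 for 10% dropout. The section gives no margin, assumed rate or power for the proportion.

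Statistical methods analyses categorical outcomes with a chi-square test at two-sided p < 0.05, and adds odds ratios with 95% confidence intervals. It names no limit against which such an interval is to be read, and no rule for combining the two primary outcomes.

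**The concern.** A non-inferiority claim needs a margin and a confidence limit to set against it. Mean NRS has a margin. The responder proportion has none, and the test named for it asks whether the arms differ. A non-significant difference in 72 patients is compatible with a large loss of responders, so it cannot be read as non-inferiority. Only a significant result in favour of end-on would settle the question, and that is not the result the design expects.

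One of the two primary hypotheses therefore has no usable decision rule. Additional studies makes a later cost-effectiveness study depend on non-inferiority being achieved, so the gap affects what happens next. A margin or success rule chosen once the data are known would carry little weight.

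**Working it through.** **1. Inputs.** From Sample size: margin 1 NRS point, SD 1.7, 36 per arm, 80% power, alpha 0.05. The documents give no responder rate for 50% relief at 3 months. The nearest figures use other definitions and times; for example, one cited study "reported a success rate (defined as greater than 80% pain relief) of 68 and 51% at 6 and 12 months post-procedurally". The true rate is therefore assumed equal in both arms at 50–70%, with 80% as a further case. The responder margin is also assumed.

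**2. The plan's own figure.** For mean NRS, n per arm = 2 × SD² × (z_alpha + z_power)² / margin².
- One-sided 0.05: 2 × 1.7² × (1.645 + 0.842)² = 35.7, so 36 per arm and 72 in total. This reproduces the plan.
- One-sided 0.025, which matches the two-sided 0.05 stated: 2 × 1.7² × (1.960 + 0.842)² = 45.4, so 46 per arm and 92 in total. This does not. At 36 per arm the power would be 70%.

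This mismatch is a separate issue. The results below lead with one-sided 0.05, so that it is not counted against the responder outcome.

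**3. What a non-significant chi-square allows.** Suppose 22/36 respond with the parallel technique (61.1%) and 15/36 with end-on (41.7%).
- Pooled SE = √(0.514 × 0.486 × 2/36) = 0.118, so z = 0.194/0.118 = 1.65 and p is about 0.10: not significant.
- The 95% CI, with unpooled SE 0.116, is −19.4 ± 22.7, or about −42 to +3 points. No one would call this non-inferior.

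**4. Precision.** SE = √(2p(1−p)/36).
- p = 0.5: SE 0.118, 95% half-width 23 points.
- p = 0.7: SE 0.108, 95% half-width 21 points.

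**5. A responder margin comparable to 1 NRS point.** With follow-up NRS normal (SD 1.7) and a common baseline, a 1-point worse mean lowers response from p to Φ(Φ⁻¹(p) − 1/1.7).
- p = 0.5: 0.500 − 0.278 = 22 points.
- p = 0.6: 0.600 − 0.369 = 23 points.
- p = 0.7: 0.700 − 0.475 = 23 points (22.5).

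**6. Power for the proportion at 36 per arm.** Power = Φ(m/SE − z_alpha), for p = 0.5 to 0.7.

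| Margin m | One-sided 0.05 | One-sided 0.025 |
|---|---|---|
| 20 points | 52–58% | 40–46% |
| 23 points | 62–69% | 50–57% |

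At a true rate of 80%, the 20-point figures are 68% and 56%. The margin that would give 80% power is (z_alpha + 0.842) × SE. Over rates of 50–80% this is 29 down to 23 points at one-sided 0.05, and 33 down to 26 points at one-sided 0.025.

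**7. If both outcomes must pass.** Trials were simulated with baseline mean 7, follow-up mean 3.2, SD 1.7 and baseline–follow-up correlation 0.3, which gives a response of about 57%. Baseline SDs from 0.8 to 1.5 were tried and made little difference. At one-sided 0.05, joint power is about 52% for a 20-point margin and about 60% for a 23-point margin.

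**The case against.** Three objections have force.

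*A margin may sit in a document not shown.* It may. But the article does fix, justify and size one primary outcome, while for the other it states a non-inferiority hypothesis and names a test that does not address it. That conflict is in the text. If a margin exists elsewhere, the article's analysis must be brought into line with it.

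*The plan never says that both outcomes must pass.* This is correct. Hypotheses is in the plural, and Objectives and Outcomes list two separate comparisons. A reader might infer a single joint claim from the wording, but no section states one, so joint power is conditional on that reading. If either outcome were enough, the issue would be two unadjusted chances of success, once a margin for the second had been supplied. Because responder status is derived from the same NRS score, the resulting inflation would be smaller than for two independent tests. The margin is missing under both readings.

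*The power shortfall rests on assumed rates and margins.* This also stands. A reader might go to a 10-point margin, where power at one-sided 0.025 is only 13–15% for rates of 50–70%, and call the trial badly underpowered. The documents do not support that margin, and it is far stricter than the 22–23 points that match the accepted NRS tolerance at these rates. Likewise, the joint power of about 38% at one-sided 0.025 with a 20-point margin includes the separate alpha mismatch of step 2. With a rate near 80% or a margin of 23–29 points, most or all of the shortfall at one-sided 0.05 disappears.

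**Conclusion.** The point holds in this form: a named primary non-inferiority outcome has no margin, no success rule and no part in the sample size, and its planned chi-square test cannot establish non-inferiority when it is non-significant. This follows from the text alone and needs no assumption. The stated 80% power applies to mean NRS only.

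The size of the shortfall is conditional. With 36 evaluable per arm, equal true rates of 50–70% and margins of 20 to 23 points, power for the proportion is 52–69% at one-sided 0.05 and 40–57% at one-sided 0.025. If both outcomes must pass, joint power is about 52–60% at one-sided 0.05. The documents do not support the stronger statement that the trial has a defined joint claim for which it is known to be badly underpowered. The defect still concerns the primary conclusion and should be settled before unblinding.

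**What to change.** **Preferred.** Before unblinding, name mean NRS at 3 months as the single primary non-inferiority outcome, since it is the only one with a margin and a sample size. Make the responder proportion at 3 months the first secondary outcome, reported as a risk difference with 95% CI and without a non-inferiority claim. Align Objectives, Hypotheses, Outcomes and Statistical methods accordingly.

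*Cost:* a protocol amendment and a registry update, with no extra patients. Recruitment began in March 2023, so this is a change to a primary outcome after the trial started. It should be dated, justified and reported as such, with a statement that it was made without knowledge of results by arm.

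**If the proportion stays co-primary.** State that both outcomes must pass. Fix and justify a margin on the risk-difference scale now. Replace the chi-square test with the confidence limit for the risk difference read against that margin. Restate the power for the joint claim at the planned size.

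*Cost:* either openly lower power at 72 evaluable, or more patients. For the proportion alone with a 20-point margin, 80% power at one-sided 0.05 needs 156 evaluable in total at a 50% rate, 130 at 70% and 100 at 80%.

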### Statistical methods

A statistician will be consulted to assist in data analysis and interpretation. Descriptive information for the sample’s study measures will include frequency distributions or proportions for categorical variables and means (standard deviations) or medians (interquartile ranges) (if non-normally distributed) for the continuous variables. To compare data between the two groups, categorical outcomes will be analyzed with the chi-square test and continuous variables will be analyzed with independent *t*-tests (or Wilcoxon rank sum test, as appropriate). A two-sided *p*-value of < 0.05 will be considered statistically significant. Both intention-to-treat (based on study arm allocation) and per-protocol (based on the participants who adhered to the study protocol and provided data at study outcome time points) analysis will be performed and reported.

Correlation between reduction in pain and improvement in function will be evaluated with a longitudinal model of changes from baseline to 3-month, 6-month, and 12-month follow-ups. An intention-to-treat strategy will be used for all analyses. Differences in treatment effects and 95% confidence intervals for pain and secondary outcome scores will be calculated using chi-square and odds ratios for dichotomous variables, and ANOVA (with *t*-tests for pairwise comparisons) and Mann–Whitney for continuous variables, as indicated. A set of logistic regression models for categorical outcome at 3 months will be created using variables hypothesized to have an effect on treatment (gender, intensity of pain, nature of injury), as well as those found to have a *p*-value less than 0.20 in univariate analysis. A secondary analyses based on data from participants who undergo unilateral versus bilateral RFN with each of the two study treatments is also planned. Missing data will be imputed using the “last observation carried forward” approach if at least 80% of the outcome data is available for the participant. All analyses will be performed using the SPSS program.

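### The secondary hypotheses claim non-inferiority, but no margin is given for them and the stated tests of a difference cannot establish it

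*Protocol article*

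**What the plan says.** **Hypotheses.** "The secondary hypotheses are that end-on lesioning for RFN of the CMBN is non-inferior to the parallel conventional technique". The domains and timing follow: "function, quality of life, sleep, adverse effects of the interventions, analgesic intake at specified time points within 1 to 12 months". No margin is attached to any of them.

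**Sample size.** One margin appears: "The chosen non-inferiority margin of less than or equal to 1 point (10%) is reasonable". It concerns the difference at 3 months "in the mean NRS pain intensity scores (0–10 scale) between the two treatment groups being less than or equal to 1 point", which is a primary outcome.

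**Statistical methods.** For the comparison of the groups, "categorical outcomes will be analyzed with the chi-square test and continuous variables will be analyzed with independent" *t*-tests, or Wilcoxon rank sum tests where appropriate. The rule for a conclusion is: "A two-sided *p*-value of < 0.05 will be considered statistically significant". The same section also plans 95% confidence intervals for pain and secondary outcome scores, with odds ratios, ANOVA and Mann–Whitney named as tools. It does not say what limit an interval must exclude before non-inferiority is concluded.

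**Objectives and Outcomes.** The secondary objectives are worded neutrally, as things to compare or assess. Nearly all the secondary outcomes are defined as between-group differences. Neither section mentions non-inferiority for them.

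**The concern.** A non-inferiority hypothesis needs a null of the form: the new technique is worse by at least a stated amount. Chi-square, *t* and rank-sum tests at two-sided 0.05 address a different null, that the groups do not differ. Rejecting that null shows a difference. Failing to reject it shows nothing about how much worse the new technique might be.

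The hypotheses and the stated decision rule therefore do not fit together. At stake is what the trial may conclude about disability, sleep, quality of life, analgesic use and adverse effects. A reader who sees non-inferiority hypotheses next to a column of p-values above 0.05 could take those p-values as support. With about 36 per arm, such p-values are common even when the end-on arm is truly worse.

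**Working it through.** **1. The plan's own figure.** Inputs from Sample size: margin 1, SD 1.7, 80% power, 36 per group. With n per arm = 2 × SD² × (z_α + z_β)² / margin²:
- one-sided 0.05: 2 × 2.89 × (1.645 + 0.842)² = 35.7, so 36 per arm, as stated;
- two-sided 0.05 (one-sided 0.025): 2 × 2.89 × (1.960 + 0.842)² = 45.4, so 46 per arm.

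The stated 36 thus matches a one-sided 0.05 test, not the two-sided test that the text names. That is a separate matter. Here 36 is used only as the analysed group size; 72 / 0.90 = 80 recruited agrees with the stated 10% dropout. No sample size is stated for any secondary outcome.

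**2. Hypothesis against test.**

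| Element | Stated for secondary outcomes |
|---|---|
| Hypothesis | non-inferiority |
| Margin | none |
| Tests | chi-square; *t* or Wilcoxon/Mann–Whitney (difference tests) |
| Decision rule | two-sided p < 0.05 |
| Intervals | 95%, with no limit to compare with |

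Nothing in the right-hand column leads from the data to a non-inferiority conclusion.

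**3. How often a truly worse arm is non-significant, 36 per arm.** The document gives no rates or standardised effects for secondary outcomes, so the deficits below are assumptions.

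*Continuous outcome, two-sided t-test, 70 df.* The standard error of the difference in SD units is √(2/36) = 0.236. For a deficit of 0.4 SD the noncentrality is 0.4 / 0.236 = 1.70. The noncentral *t* gives power 0.388, so p > 0.05 about 61% of the time.

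*Binary outcome, uncorrected chi-square, exact enumeration of both binomials.* Power is 0.235 for 60% v 45% and 0.383 for 60% v 40%, so p > 0.05 about 77% and 62% of the time.

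Range over other assumed values:

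| True deficit | P(p > 0.05) |
|---|---|
| 0.3 SD | 76% |
| 0.4 SD | 61% |
| 0.5 SD | 45% |
| 1/1.7 = 0.59 SD (size of the NRS margin) | 31% |
| 10 points, control rate 50–70% | 85–87% |
| 15 points, control rate 50–70% | 74–77% |
| 20 points, control rate 50–70% | 59–62% |

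**4. What the planned intervals can show.** The 95% half-width for a continuous outcome is 1.994 × 0.236 = 0.47 SD. For proportions near 50% it is 1.96 × √(2 × 0.5 × 0.5 / 36) = 0.231, and near 60% it is 0.226, so about 23 percentage points. Even an observed difference of zero would leave deficits of that size inside the interval.

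**The case against.** The strongest reply is that nothing in the protocol says a non-significant result will be taken as non-inferiority. Statistical methods also plans 95% confidence intervals for secondary outcome scores, and an interval is the usual vehicle for a non-inferiority conclusion. Margins and interval rules for secondary outcomes are commonly left to a full protocol or analysis plan, which is not shown. Objectives and Outcomes already treat these endpoints as comparisons, so little more than one sentence is out of line.

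Much of this stands. A reader might infer that p > 0.05 is the trial's intended or only route to a secondary non-inferiority claim. The documents do not say so, and the planned intervals count against it. The absence of secondary margins, taken alone, is not the point either. What remains is that the article itself states a hypothesis and a decision rule that do not match. A later document could add margins, but the two sections would still disagree until one is reworded.

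Two further inferences should be resisted.
- The Sample size section says that adverse effects may be fewer with the end-on technique. That does not contradict a hypothesis that they are no worse.
- Discomfort, procedure time and radiation are not in the list of secondary non-inferiority hypotheses. They are already framed as comparisons in Objectives and Outcomes, so they need no rewording on this account.

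On priority, these are supportive outcomes, and the claim on the primary outcomes matters more to the trial's conclusion. That limits the weight of the point but does not answer it.

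**Conclusion.** The point holds as a mismatch between Hypotheses and Statistical methods. The document states non-inferiority for five secondary domains, gives no margin for any of them, and decides by two-sided tests of a difference. The planned 95% intervals have no limit to be judged against. As written, the analysis cannot establish these hypotheses, and a non-significant result could be misread as doing so.

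The percentages show how weak such a misreading would be: about 77% for 60% v 45%, 62% for 60% v 40% and 61% for 0.4 SD. They rest on 36 analysed per arm and on assumed deficits. They are not error rates of a rule that the protocol has adopted.

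**What to change.** In Hypotheses, replace the secondary non-inferiority sentence with text to this effect: the two techniques will be compared on disability, sleep, health-related quality of life, analgesic use and adverse effects at the scheduled follow-ups; each result will be reported as a between-group difference with its 95% confidence interval; no non-inferiority claim will be made for these outcomes, and p > 0.05 will not be taken as evidence of non-inferiority. This agrees with the neutral wording in Objectives and uses intervals that Statistical methods already plans. It should be done before unblinding.

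The cost is a wording amendment, with no new data, participants or tests. The sponsor gives up secondary non-inferiority claims that the stated analysis could not support.

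The alternative is to name particular secondary outcomes, each with a justified margin and an interval rule. It is valid but would be weak at this size. With no true difference and one-sided 0.025, an assumed margin of 0.5 SD needs 63 per arm for 80% power, and 36 per arm gives 56%. An assumed margin of 20 percentage points (rates 50–70%) needs 83–99 per arm, and 36 gives 40–46%.
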